### Procedures

2.4

Participants will be recruited from the Houston community through multimedia platforms (university listservs, flyers, etc.). Interested participants will complete an online screener via Qualtrics, an online data collection platform. Participants who qualify will be contacted by trained study staff who will describe the study and schedule the baseline visit. Upon arrival to the lab, participants will provide informed consent and be assessed regarding trauma history, PTSD symptomatology, substance use, and the presence of current/past bipolar or psychotic disorder, as determined by the MINI-International Neuropsychiatric Interview. A urine drug screen will be implemented at baseline to identify current substance use (not used for exclusion).

Once eligibility is confirmed, participants will be randomly assigned (equally; 50 participants per condition, using a simple randomization design) to AP-PFI or C-PFI and complete the intervention/comparison condition on laboratory computers. Participants will then complete a post-intervention assessment. Online follow-up assessment will include similar surveys and will be scheduled 1-week and 1-month after completing the intervention conditions. Participants will be compensated $25 for completing the in-person baseline assessment and $35 and $40 for completing the 1-week and 1-month follow-up surveys, respectively, for a total of $100 in eGift cards. All study procedures were approved by the University Institutional Review Board and all study measures and assessment procedures are outlined in Table 1 and Fig. 1.

**Table 1 tbl1:** Study measures and timepoints.

Measures	Items	Assessment Timepoint				
		**Screen**	**Baseline**	**Post**	**1-Week**	**1-Month**
Demographics Questionnaire	**20**	**X**				
Urinalysis drug screening	**N/A**		**X**			
Breath analysis	**N/A**		**X**			
MINI-International Neuropsychiatric Interview	**Variable**		**X**			
Treatment Credibility/Expectancy Questionnaire	**6**			**X**		
Modified Satisfaction with Treatment	**7**			**X**		
Alcohol Ladder	**1**		**X**	**X**	**X**	**X**
Modified Alcohol Use Disorders Identification Test	**3**–**10**	**X**	**X**		**X**	**X**
The Short Inventory of Problems	**15**		**X**		**X**	**X**
Alcohol Urges Questionnaire	**8**		**X**	**X**	**X**	**X**
Timeline Follow-Back	**30**		**X**		**X**	**X**
Life Events Checklist for *DSM-5*	**17**	**X**	**X**		**X**	**X**
Modified PTSD Checklist for *DSM-5*	**20**	**X**	**X**		**X**	**X**

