### Data analytic plan

2.7

Data will first be examined for multivariate normality; the maximum likelihood (ML) estimator will be used if data are approximately normal, and robust maximum likelihood will be used if the data are not multivariate normal. Categorical outcomes (i.e., hazardous drinking status) will be estimated using the mean and variance adjusted weighted least squares estimator when appropriate. Missing data will be handled using direct ML techniques within MPlus [60] under a missing at random assumption [61]. Differences in key baseline characteristics between randomly assigned intervention condition groups will be assessed and significant characteristics will be used as covariates to determine the influence of any potential randomization failures on results. Latent growth models (LGM) will be used to model linear trajectories of change in outcomes. Evaluation of LGM model fit will be examined using fit diagnostics (i.e., standardized residuals) and fit statistics (i.e., root mean square error of approximation) following recommended cutoffs [62].

*Aim 1.* To evaluate the feasibility and acceptability of AP-PFI vs. C-PFI, initial metrics of feasibility and efficacy will be examined, including (1) recruitment/retention rates throughout the duration of the study, (2) intervention acceptability at post-intervention, intervention utilization at 1-week and 1-month follow-up, and (3) initial efficacy at post-intervention, 1-week, and 1-month follow-up. Retention between conditions will be assessed utilizing binary logistic regression to examine condition (0 = control; 1 = PFI) as a predictor of each follow-up completion (0 = missed; 1 = completed). Effect sizes will be calculated with Cohen's *d* for frequency and proportions [i.e., of completed follow-ups; 63]. Intervention acceptability will then be evaluated with condition as a predictor of acceptability items (i.e., TCEQ, SAT); theoretically relevant variables such age, sex, and racial/ethnic minority status will be included as covariates. Cohen's *d* for mean differences will be calculated [63].

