*Aim 2*. Hypotheses for Aim 2 (i.e., efficacy and intervention effects) will be examined using regression-based approaches, effect sizes (with 95% confidence intervals [CI]), and LGM using Mplus [60,62,64]. We will first estimate between-group differences with regression-based approaches by calculating odds ratios or Cohen's *d* effect sizes (with 95% CI) for the primary post-intervention outcomes (i.e., motivation/intention to reduce drinking) and primary 1-week and 1-month follow-up outcomes (i.e., change in rates from hazardous to non-hazardous drinking, frequency and quantity of alcohol consumption and negative consequences of drinking, and PTSD symptomatology). We will then conduct a series of conditional LGMs to examine the impact of intervention condition over time on the 1-month follow-up outcomes. A dummy code representing intervention condition will be included in the model as a predictor of the slope factor to quantify the effect of the PFI on the outcomes.

*Exploratory aim 3*. Similar modeling procedures will be used to test mechanisms of change. After conducting univariate LGM to explore changes in the putative mediators (i.e., motivation/intention to reduce drinking and levels of AS) as a function of condition, we will conduct a series of parallel process LGMs to examine how changes in the mechanisms relate to changes in primary follow-up outcomes at each assessment point. The effects of changes in the mechanisms of change on the outcomes will be examined by specifying the slope factor for each potential variable as a predictor of the slope factor for each outcome. The indirect effects of condition on outcomes via the hypothesized mechanisms will be evaluated by bootstrapped CI. Further, given the purported interaction effect of sex and a family history of AUD, dummy coded variables (0 = female, 1 = male; 0 = no history, 1 = history; respectively) will be included as additional predictors of slope in the LGM parallel process models.

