*Sample size and power.* Power calculations were performed to statistically determine the target sample size of *N* = 100 for this pilot study**.** Small-to-moderate effects of the AP-PFI on primary follow-up outcomes and the hypothesized mechanisms are expected, and moderate-to-large associations (*r* > .30) between changes in the mechanisms and changes in 1-month follow-up outcomes are expected. Monte Carlo simulation studies [65] with 10,000 repetitions to identify the sample sizes necessary to detect effects indicated that the targeted sample size of 100 participants would yield 80% power to detect small-to-moderate effects for primary study aims at alpha = .05. Additionally, extant guidelines for pilot RCT designs [66] indicate that a targeted sample size of 100 participants would yield 90% power to detect small-to-moderate effects for study aims set at alpha = .05. Thus, the target sample size is well above current guidelines for pilot studies in clinical research [67].

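### Covariates are chosen by baseline significance tests, and the first-step Aim 2 regressions name no adjustment for the outcome's own baseline

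*Protocol article*

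**What the plan says.** The general part of section 2.7 (Data analytic plan) has key baseline characteristics compared between the arms. Those differences "will be assessed and significant characteristics will be used as covariates to determine the influence of any potential randomization failures on results". It gives no test level and no list of the key characteristics, and it does not say whether the adjusted result is the main result or a supporting one.

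Aim 2 in the same section has two steps. First: "We will first estimate between-group differences with regression-based approaches by calculating odds ratios or Cohen's" *d*, with 95% confidence intervals. This covers motivation to reduce drinking at post-intervention, and drinking, consequences and PTSD symptoms at 1 week and 1 month. No covariate is named for these regressions. Second come conditional LGMs for the 1-month outcomes, with condition entered as a predictor of the slope factor.

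Table 1 marks the Alcohol Ladder, AUDIT, SIP, AUQ, TLFB, PCL-5 and SSASI at baseline. Allocation is "50 participants per condition, using a simple randomization design" (section 2.4), with no stratification factor named. Covariates are named in advance only for the Aim 1 acceptability analyses: age, sex and racial/ethnic minority status.

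**The concern.** If randomization was carried out properly, every baseline difference is chance. A significance test between the arms then cannot reveal a failed randomization, and it says nothing about whether a variable predicts the outcome. A rule built on it can bring in variables of no prognostic value because they happened to differ, and it leaves out strong predictors that happened to balance. The covariate set is also unknown until the data have been seen.

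The strongest predictor of a follow-up score is usually the same score at baseline, and this trial collects it. If the first-step regressions leave it out, the Cohen's *d* estimates are less precise than the data allow. With 100 participants and an expectation of only small-to-moderate effects, that precision matters.

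**Working it through.** **Inputs from the protocol article.** N = 100, 50 per arm (section 2.4); alpha .05 (section 2.7, Sample size and power). The effect is given only in words: "Small-to-moderate effects of the AP-PFI on primary follow-up outcomes and the hypothesized mechanisms are expected".

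**Assumptions.** Two-sided tests; d from 0.2 to 0.5; baseline–follow-up correlation r from 0.3 to 0.7; baseline tests at .05; continuous outcome; no dropout.

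**1. The plan's own figure.** The article says that "the targeted sample size of 100 participants would yield 80% power to detect small-to-moderate effects", by Monte Carlo simulation, and gives 90% on the strength of pilot-trial guidelines. With no numeric effect, neither can be reproduced. For a plain two-group comparison in SD units, SE = √(2/50) = 0.200, and power ≈ Φ(d/SE − 1.96):

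- d = 0.2: 16.9%
- d = 0.35: 41.7%
- d = 0.5: 70.5%

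80% power needs d = (1.96 + 0.84) × 0.200 = 0.56.

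**2. How often the rule fires by chance.** With k independent tests at .05, P(at least one significant) = 1 − 0.95^k: 23% for k = 5, 40% for k = 10, 54% for k = 15. Any single variable, including an outcome's own baseline, is picked about 5% of the time.

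**3. What own-baseline adjustment gives.** The variance is multiplied by 1 − r², so SE = 0.200 × √(1 − r²).

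| r | Variance factor | SE | d at 80% power | Power, d = 0.35 | Power, d = 0.5 | Equivalent N = 100/(1 − r²) |
|---|---|---|---|---|---|---|
| none | 1.00 | 0.200 | 0.56 | 41.7% | 70.5% | 100 |
| 0.3 | 0.91 | 0.191 | 0.535 | 45.0% | 74.6% | 110 |
| 0.5 | 0.75 | 0.173 | 0.485 | 52.4% | 82.3% | 133 |
| 0.7 | 0.51 | 0.143 | 0.40 | 68.8% | 93.8% | 196 |

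**4. What the rule gives.** Simulation, 20,000 trials per setting, with baseline entered only if the arms differ on it at p < .05:

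| r | Power at d = 0.5: unadjusted | Under the rule | Always adjusted | Type I error under the rule |
|---|---|---|---|---|
| 0.5 | 69.8% | 70.8% | 81.1% | 4.2% |
| 0.7 | 70.1% | 71.9% | 93.5% | 3.6% |

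The rule recovers almost none of the available precision. Its type I error lies a little below 5%.

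**5. The LGM step.** Assume that baseline is the first wave, as Table 1 suggests, with waves at 0, 1 and 4.35 weeks, compound symmetry and a linear effect. The SE of the 1-month difference is:

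| r | Unadjusted | Own-baseline adjustment | LGM, condition on slope only | LGM, condition also on intercept |
|---|---|---|---|---|
| 0.5 | 0.200 | 0.173 | 0.172 | 0.191 |
| 0.7 | 0.200 | 0.143 | 0.140 | 0.148 |

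With condition on the slope only, the LGM already has the precision of baseline adjustment. Part of it is lost if the intercept may differ by arm.

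**6. Odds ratios.** The factor 1 − r² does not apply. In an illustrative logistic simulation (50 per arm, conditional log odds ratio 0.8, covariate slope 1.0), the mean SE was 0.41 unadjusted and 0.46 adjusted, and power was 41% and 44%.

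**The case against.** A reader might infer that the plan as a whole ignores each outcome's baseline. The document does not support that. Condition acts on the slope of growth models that appear to start at baseline, and step 5 shows that this recovers the precision. Nor does the article rank the first-step regressions above the LGMs, so those regressions cannot be called the headline analysis. The LGM is not a full substitute, though. The Aim 2 LGMs are directed at the 1-month outcomes, whereas the post-intervention motivation contrast and the 1-week contrasts come from the regressions.

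A second objection is that silence on regression covariates is normal in an article and may be settled in an analysis plan that is not shown. That is fair for the missing own-baseline covariate taken alone. It does not excuse the selection rule, which the article states outright and which is the only covariate rule that reaches the Aim 2 regressions.

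Third, the stated purpose of judging the influence of randomization failures may describe a sensitivity analysis. This reading is open. The article does not settle it, and the tests are uninformative for that purpose too.

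Fourth, the gain depends on r, and a high r is not assured. Eligibility cut-offs truncate the AUDIT, PCL-5 and ASI-3, and the PCL-5 and TLFB recall windows differ between baseline and follow-up. This stands and is why a range is shown. At r = 0.3 the gain is about 4 power points (70.5% to 74.6%).

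Finally, one might expect data-driven selection to inflate false positives. The simulation shows the opposite: the rule is slightly conservative.

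**Conclusion.** The point holds in a limited form. The stated rule selects covariates by chance imbalance and should go. The possible loss of precision is confined to continuous outcomes in the first-step Aim 2 regressions. At d = 0.5 the rule leaves power at about 71–72%, against 81% with own-baseline adjustment at r = 0.5 and 94% at r = 0.7 (simulated). That is a loss of roughly 10 and 22 points; at r = 0.3 it is only a few points.

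These sizes rest on assumed values of r and d, a two-sided .05 test, no dropout, and regressions that in fact carry no baseline covariate, a matter on which the article is silent. The LGM comparison also assumes that baseline is the first wave. No inflation of type I error is shown, and no precision gain is claimed for odds ratios.

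**What to change.** In section 2.7:

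- Delete the rule that turns significant baseline differences into covariates.
- State that each first-step Aim 2 regression adjusts for the baseline value of its own outcome, plus any short covariate list fixed in advance.
- For hazardous-drinking status, use the continuous baseline AUDIT-C score. Everyone must screen as a hazardous drinker to enter, so status at entry cannot serve as a covariate.
- State that baseline is the first LGM wave and that condition has no effect on the intercept.
- If a model adjusted for observed imbalance is kept, label it a sensitivity analysis only.

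The cost is a change of wording. All the baseline measures needed are already in Table 1, so no new data are required.

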### Specific aims and hypotheses

2.2

The first aim of this project will be to evaluate the feasibility and acceptability of a brief, single-session, integrated, computer-based PFI (AP-PFI) based on participant ratings of satisfaction and the perceived credibility/expectancies of the intervention. The second aim will be to conduct a RCT to examine the efficacy and intervention effects on drinking, AS, and PTSD outcomes of AP-PFI, versus C-PFI, across the post-intervention and 1-week and 1-month follow-ups. The third aim will be to explore mechanisms of change and moderators.

Regarding the first aim (feasibility and acceptability), it is hypothesized that participants randomized to AP-PFI (vs. C-PFI) will evince greater satisfaction and perceived credibility/expectancies of the intervention. Regarding the second aim (efficacy and intervention effects), it is hypothesized that participants randomized to AP-PFI (vs. C-PFI) will evince (1) greater motivation/intention to reduce drinking, (2) lower levels of AS, (3) lower frequency and quantity of alcohol consumption, (4) reduced negative consequences of drinking and alcohol-related craving, and (5) lower PTSD symptom severity at 1-week and 1-month follow-up. Additionally, regarding the third aim, it is hypothesized that the effects of AP-PFI (vs. C-PFI) on post-intervention outcomes will be mediated by greater motivation/intention to reduce drinking and lower levels of AS. It is also hypothesized that the effects of AP-PFI (vs. C-PFI) on post-intervention, 1-week, and 1-month follow-up outcomes will be moderated by biological sex (i.e., larger magnitude of effect among female participants, relative to male participants) and family history of AUD (i.e., larger magnitude of effect among participants with a family history of AUD).

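### As written, the moderator analysis estimates main effects of sex and family history on slope, so it does not test the stated hypotheses that the intervention effect differs between these groups

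*Protocol article*

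**What the plan says.** Section 2.2 (Specific aims and hypotheses) states that the effects of AP-PFI versus C-PFI on the post-intervention, 1-week and 1-month outcomes "will be moderated by biological sex (i.e., larger magnitude of effect among female participants, relative to male participants"), and also by "family history of AUD (i.e., larger magnitude of effect among participants with a family history of AUD"). Both statements are directional and concern the size of the between-arm effect.

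Section 2.7 (Data analytic plan) gives the models. Under Aim 2, "A dummy code representing intervention condition will be included in the model as a predictor of the slope factor". Under Exploratory aim 3, the reason for bringing in the moderators is "given the purported interaction effect of sex and a family history of AUD". The variables are coded "0 = female, 1 = male; 0 = no history, 1 = history; respectively", and they "will be included as additional predictors of slope in the LGM parallel process models".

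The article mentions no product of condition with either variable, no multiple-group model and no contrast of subgroup effects. The power paragraph of Section 2.7 gives no figure for moderation; its 80% claim is tied to the primary aims.

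**The concern.** Moderation means that the condition effect takes different values at different levels of the moderator. In a growth model this needs a condition-by-moderator term, or separate condition effects by group. The terms named here are the moderators themselves, placed beside condition as further predictors of the slope. In form this is covariate adjustment, as the same section uses for sex in the Aim 1 acceptability models.

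Two things are at stake within Aim 3. A sex or family-history coefficient could differ from zero because the groups change at different rates whatever they receive, and it would carry no information on whether AP-PFI works better in one of them. And the quantity that Section 2.2 makes a prediction about would not be estimated.

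**Working it through.** **1. What the printed model implies.** Write C for condition, S for sex (1 = male) and H for family history (1 = yes). The stated predictors of slope give

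slope = a + b1·C + b2·S + b3·H + error.

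The effect of condition is b1 for women and men, with or without a family history. The difference in effect between subgroups is zero by construction. The parallel-process version adds a path from the mediator slope to the outcome slope. With additive predictors, the direct and indirect effects of condition are still the same in every subgroup.

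The Section 2.2 hypotheses need

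slope = a + b1·C + b2·S + b3·H + b4·C·S + b5·C·H + error,

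where b4 is the effect in men minus the effect in women, and b5 is the effect with a family history minus the effect without.

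**2. Why b2 cannot stand in for b4.** The document gives no subgroup effects, so these cell means are assumed. They are in SD units, higher is better, with equal arms and equal numbers of women and men.

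| | Women AP-PFI | Women C-PFI | Men AP-PFI | Men C-PFI |
|---|---|---|---|---|
| A: effect 0.7 in women, 0 in men | 0.70 | 0 | 0 | 0 |
| B: effect 0.35 in both, women 0.35 better throughout | 0.70 | 0.35 | 0.35 | 0 |

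- Sex coefficient of the additive model (men minus women, averaged over arms): A, 0 − 0.35 = −0.35; B, 0.175 − 0.525 = −0.35.
- Condition coefficient of the additive model: A, 0.35 − 0 = 0.35; B, 0.525 − 0.175 = 0.35.
- Interaction (effect in men minus effect in women): A, 0 − 0.70 = −0.70; B, 0.35 − 0.35 = 0.

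The additive model returns the same two coefficients when moderation is strong and when there is none.

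**3. Simulation.** There were 4,000 runs per scenario with N = 100, 50 per arm, an assumed moderator share of 0.5, and a continuous outcome in place of the latent slope. The table shows the share of runs significant at two-sided .05.

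| Scenario (assumed) | Moderator term, additive model | Interaction term |
|---|---|---|
| Moderator main effect 0.6 SD, no moderation | 84% | 5% |
| Interaction 1.0 SD, no average moderator difference | 4% | 68% |
| Neither | 5% | 5% |

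**4. What the corrected test could detect.** There is no planned figure for moderation to reproduce. The inputs are N = 100 with 50 per arm (Section 2.4: "randomly assigned (equally; 50 participants per condition, using a simple randomization design"), alpha of .05 (Section 2.7; two-sided is assumed, since sidedness is not stated), and an assumed share p of participants at one level of the moderator.

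SE of the interaction = sqrt(4/(N·p) + 4/(N·(1 − p))); detectable difference at 80% power = (1.960 + 0.842) × SE.

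- p = 0.5: SE = sqrt(0.08 + 0.08) = 0.400; detectable 1.12 SD.
- p = 0.4: SE = sqrt(0.100 + 0.067) = 0.408; detectable 1.14 SD.
- p = 0.3: SE = sqrt(0.133 + 0.057) = 0.436; detectable 1.22 SD.

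For comparison, a plain two-arm contrast on the same basis detects 2.802 × sqrt(2/50) = 0.56 SD, half the value at p = 0.5. At p = 0.5, power is about 7%, 14% and 24% for interactions of 0.2, 0.35 and 0.5 SD. For the 0.7 SD of case A, the normal approximation gives Φ(0.7/0.40 − 1.96) = Φ(−0.21), or about 42%.

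**The case against.** The best defence is that this is a condensed article. The hypotheses are stated correctly as differences in effect, the analysis sentence itself names an interaction, and nothing says that product terms are excluded. A fuller protocol or analysis plan may contain them. That lowers confidence about what the sponsor will finally run. It does not rescue the sentence, which names the variables, their coding, their role and the host model, and so states a model rather than leaving one unstated. The reference to an interaction could even be read as sex by family history, and no such product is given either.

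It is also fair to say that the aim is exploratory, the trial is a pilot, and the wording can be put right at any time before analysis. This stands, and it limits the severity.

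The numbers are illustrative. Subgroup shares and effects are assumed, and a complete continuous outcome stands in for a latent slope with data missing at random. Repeated measures, measurement error and attrition could move the detectable difference either way.

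A reader might go further and infer that a significant sex coefficient will be reported as moderation. The article does not say how that coefficient will be interpreted, so this is a risk and not something the plan states.

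**Conclusion.** The point holds. The model printed under Exploratory aim 3 does not estimate the condition-by-sex or condition-by-family-history differences hypothesized in Section 2.2. This follows from the form of the model and needs no assumption about effect sizes.

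It should be fixed, but the trial does not depend on it. A reader might infer that the efficacy evaluation is compromised. The document does not support that: Aim 1, the Aim 2 comparison of arms, randomization and data collection do not rest on this sentence.

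The detectable interaction of about 1.1 to 1.2 SD at 80% power rests on N = 100 with complete data, a simple continuous outcome, two-sided alpha of .05 and an assumed split between 50/50 and 30/70. It supports presenting the moderator results as estimates with intervals. It is not a threshold to write into the protocol.

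**What to change.** Replace the moderator sentence under Exploratory aim 3 so that condition, sex, family history, condition × sex and condition × family history all predict the outcome slope. An equivalent choice is a multiple-group growth model for each moderator with a test of equal condition effects across groups. Report each interaction, and the AP-PFI versus C-PFI effect within each level, with 95% confidence intervals. Label them exploratory and present them as estimates.

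Whether the terms sit in the single-outcome or the parallel-process growth models is the sponsor's choice, provided that the condition-by-moderator difference is estimated.

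The cost is about one sentence of wording and two extra model terms. No new data are needed: the demographics questionnaire at screening covers sociodemographic factors and family history (Section 2.6.1). Section 2.1 describes the trial as still recruiting, so the change can be made before analysis.

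### The protocol attaches both 80% and 90% power to the same N, alpha and verbal effect, and neither holds across d = 0.2 to 0.5 for the planned between-group contrasts

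*Protocol article*

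**What the plan says.** The Sample size and power paragraph of section 2.7 sets the expectation in words: "Small-to-moderate effects of the AP-PFI on primary follow-up outcomes and the hypothesized mechanisms are expected". It then makes two claims.

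- From "Monte Carlo simulation studies [65] with 10,000 repetitions to identify the sample sizes necessary to detect effects", it concludes that "the targeted sample size of 100 participants would yield 80% power to detect small-to-moderate effects for primary study aims at alpha = .05".
- From published pilot-trial guidelines, it concludes that "a targeted sample size of 100 participants would yield 90% power to detect small-to-moderate effects for study aims set at alpha = .05".

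The paragraph gives no numerical treatment effect, effect metric, sidedness, model or correlation. Its one number on an effect scale, r > .30, concerns the association between change in the mechanisms and change in the outcomes, not the effect of condition.

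Elsewhere the article fixes the design and the contrasts. Section 2.4 allocates "50 participants per condition, using a simple randomization design". Under Aim 2, section 2.7 plans between-group differences as odds ratios or Cohen's d with 95% confidence intervals, followed by growth models in which "A dummy code representing intervention condition will be included in the model as a predictor of the slope factor". The Introduction lists satisfaction and credibility/expectancy among the primary outcomes, and section 2.2 hypothesises that the arms differ on them.

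**The concern.** One combination of N, alpha and effect can have only one power for a given test. The paragraph gives two and names nothing (test, outcome or effect value) that separates them. The second sentence also drops the restriction to primary aims, so read literally its 90% extends to the exploratory mechanism aim.

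Both figures also look high for a parallel comparison of 50 with 50. At that size, the effect detectable with 80% power lies above the conventional moderate value of d = 0.5.

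What is at stake is how the results are read. Efficacy is a stated objective. A null result from a trial described as having 80% or 90% power for the expected effect invites the conclusion that the integrated feedback adds nothing, when the trial may simply have missed an effect of the size the authors expect.

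**Working it through.** **Inputs from the article.** N = 100, 50 per arm (section 2.4); alpha .05 (section 2.7); contrasts as Cohen's d or odds ratio with 95% CI (section 2.7, Aim 2).

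**Assumptions.** d = 0.2 to 0.5 for small-to-moderate; a two-sided test, which matches 95% intervals; baseline-to-follow-up correlation 0.6; 20% loss (40 per arm) as a sensitivity case; control rates of 20% to 50% for the binary outcome.

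**The plan's own figures.** Neither 80% nor 90% can be reproduced, because no numerical effect is given.

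**1. Unadjusted two-sample comparison.** The noncentrality is d·√(n/2) = d·√25 = 5d. By the normal approximation, power ≈ Φ(5d − 1.96):

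- d = 0.2: Φ(−0.96) = 17%
- d = 0.35: Φ(−0.21) = 42% (41% with the t distribution)
- d = 0.5: Φ(0.54) = 70%

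The detectable d is (1.96 + 0.842)/5 = 0.56 at 80% and (1.96 + 1.282)/5 = 0.65 at 90%. The t distribution gives 0.57 and 0.66. For 80% power the number needed per arm is 2(2.802)²/d², which is 393, 129 and 63 at d = 0.2, 0.35 and 0.5. With 40 per arm, power is 14%, 34% and 60%.

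**2. Which primary outcomes have no usable baseline.** Table 1 places the credibility/expectancy and satisfaction questionnaires at the post-intervention visit only. There is no earlier value to adjust for and no repeat to model, so step 1 applies directly. Movement out of hazardous drinking is also a primary follow-up outcome. Section 2.3 requires hazardous drinking at entry, so baseline status is the same for everyone. Converting d by OR = exp(πd/√3) gives 1.44, 1.89 and 2.48. The pooled two-proportion test has

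power = Φ{[|p₂ − p₁| − 1.96√(2p̄(1 − p̄)/50)] / √([p₁(1 − p₁) + p₂(1 − p₂)]/50)}.

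- Lowest case: control rate 20%, OR 1.44, so p₂ = 26.4% and power is 12%.
- Highest case: control rate 40%, OR 2.48, so p₂ = 62.3% and power is 61%.

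**3. Outcomes with a baseline.** Adjustment divides d by √(1 − 0.6²) = 0.8, so 0.2, 0.35 and 0.5 act as 0.25, 0.44 and 0.625. Power is 24%, 58% and 87%, and the detectable d is 0.57 × 0.8 ≈ 0.45. With 40 per arm, power is 20%, 49% and 79%. Full-retention power of 80% at d = 0.35 would need a correlation of about 0.78, and at d = 0.2 about 0.93.

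**4. Growth model.** If d is defined on the slope factor, power at 50 per arm is at most 17%, 41% and 70%. It falls as the slope is measured less reliably (48% at d = 0.5 with reliability 0.6).

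**5. Mechanism path.** At N = 100, r = .30 between mediator and outcome has 86% power, and d = 0.35 on the mediator has 41%. Requiring both gives about 0.41 × 0.86 = 35%.

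**The case against.** The strongest reply is that the 80% comes from a simulation whose model and inputs are not shown, and that a t-test on assumed d values cannot refute it. Several readings do reach the stated figures:

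- A one-sided test at d = 0.5 gives 80%.
- Baseline adjustment at d = 0.5 gives 82% with correlation 0.5 and 88% by the normal approximation with 0.6.
- A change score at d = 0.5 gives 80% with correlation 0.6 and 90% with 0.7.
- A repeated-measures interaction of f = 0.10 over three timepoints with correlation 0.7 gives 81%.
- Regression f² = 0.08 gives 80%.

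So a reader might infer that N = 100 simply cannot deliver 80% or 90%. The documents do not support that: the effect has no number or metric, and d = 0.2 to 0.5 is an assumption. A reader might also infer that loss to follow-up was ignored, or that the cited guideline is wrong. Neither can be shown. The article is condensed, the attrition inputs may sit in the full protocol, and the cited source is not at hand. Aim 3 is already called exploratory, effects are already to be reported with intervals, and the trial is called a pilot throughout.

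These points limit the finding but do not remove it. The one-sided, adjusted and change-score routes work only near the top of the d range; one-sided power at d = 0.35 is 54%, and no one-sided test is stated. The f² route only changes the scale, since f² = 0.08 corresponds to d = 2√0.08 = 0.57. The repeated-measures route is not available for outcomes measured once. And the article itself prints two different powers for one description.

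**Conclusion.** The point holds in a limited form. The 80% and 90% are unreconciled as written. On the planned d or odds-ratio contrasts, neither holds across d = 0.2 to 0.5. The shortfall is clearest for outcomes without a usable baseline: 17% to 70% for satisfaction and credibility/expectancy, and about 12% to 61% for leaving hazardous drinking. For baseline-adjusted outcomes, 80% is attainable from about d = 0.45 with full retention and correlation 0.6, and is just missed at d = 0.5 (79%) with 20% loss.

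The contradiction between the two figures needs no assumption. The sizes rest on the assumed d range, two-sided testing, the correlation, the loss rate and the control rates. One qualification applies to the binary outcome: baseline status is constant, but a baseline drinking score could still serve as a covariate and recover some precision. The documents do not say how much.

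**What to change.** Keep N = 100 and replace the two power sentences with one statement of the effect detectable at 80% power, by outcome type:

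- about d = 0.57 for outcomes without a baseline;
- about d = 0.45 for baseline-adjusted outcomes if the correlation is about 0.6;
- larger values after expected loss. With 40 per arm, 2.802 × √(2/40) = 0.63 unadjusted, and 0.63 × 0.8 ≈ 0.50 adjusted.

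Name the effect metric, sidedness and model behind each value. If the simulation supports a different figure, give its numerical effect and the outcome it refers to. Either tie the 90% to a specific test and effect in this trial or remove it. Add that Aim 3 is not powered, and that a null efficacy result will be read from its confidence interval and not as evidence of no benefit.

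The change is wording only and needs no extra participants. The downside is that the stated power becomes less favourable.
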